#### Glutathione enrichment and concentration

Analysis of GSH will be performed on a LC-Isolink interface coupled to a Delta XP isotope ratio mass spectrometer (LC-IRMS) (Thermo Fisher, Bremen, Germany) using a recently developed method [13]. This highly sensitive method requires only a very small sample and does not require derivatization of the sample.

#### Glycine enrichments

The erythrocyte enrichment of ^13^C glycine will be measured by gas chromatography-mass spectrometry (GCMS) as its ethyl chloroformate (ECF) ester derivatives, using a MSD 5975 C Agilent GCMS (Agilent Technologies, Amstelveen, The Netherlands). Briefly, 25-μl aliquots of the remaining supernatant used for the GSH analysis will be acidified by adding 50 μl of 0.1 M HCl and diluted with 125 μl of distilled water. ECF derivatization of the samples will be performed according to a modified procedure of Hušek [14]. A CP-Sil 17 column (25 m × 0.25 mm id, 0.12-μm film thickness; Varian, Middelburg, The Netherlands) will be used for the separation. The samples will be measured using a selected ion monitoring mode (SIM) method. The mass fragments with a mass to charge (*m/z*) of 102.1 for unenriched (*M*)and an *m/z* 103.1 for the enriched (*M* + 1) glycine, respectively, have been selected for this purpose.

#### Calculations

The FSR_GSH_ represents the fraction of the total intraerythrocytic GSH pool that is renewed per unit of time and is expressed as %/d.

(1)$${\mathrm{FSR}}_{\mathrm{GSH}}(\%/d)=\frac{slope\;E_{[U{-}^{13}C]GSH_{t6,7,8}}}{E_{intraerythrocytic[U{-}^{13}C]glycine}}\times 24h\times 100\%\text{,}\;$$

where E stands for the enrichment expressed as MPE. The nominator (product) of this equation represents the hourly increase in [U-^13^ C]glycine bound to GSH, as calculated from the increase in enrichment between 6 and 8 h of infusion. The denominator (precursor) represents the intraerythrocytic U-^13^ C enrichment of free glycine at isotopic steady state.

Subsequently, the intravascular ASR_GSH_, which represents the absolute amount of GSH that is produced per unit of time (mg/(kg·day)), can be calculated using the following equation:

(2)$${\mathrm{ASR}}_{\mathrm{GSH}}(\text{mg}/(\text{kg}\times \text{d})={\mathrm{FSR}}_{\mathrm{GSH}}/(100\text{ × conc}.\text{ × }307\text{ × ht × }0.075)$$

where conc. is GSH concentration in mmol/l packed erythrocytes, 307 is the molecular weight of GSH, ht is hematocrit, and 0.075 is the estimated circulating volume in a preterm neonate, expressed as l/kg.

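### Equation 2 as printed divides by the glutathione pool instead of multiplying by it, so the absolute synthesis rate has the wrong unit and moves the wrong way with concentration and hematocrit

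*Protocol article*

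**What the plan says.** All of this is in the Protocol article, section Calculations, unless noted.

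- FSR "represents the fraction of the total intraerythrocytic GSH pool that is renewed per unit of time and is expressed as %/d".
- ASR is the quantity "which represents the absolute amount of GSH that is produced per unit of time (mg/(kg·day)), can be calculated using the following equation". Equation 2 then sets ASR equal to FSR divided by a bracket that contains "100\text{ × conc}.\text{ × }307\text{ × ht × }0.075".
- The terms are defined directly below: "where conc. is GSH concentration in mmol/l packed erythrocytes, 307 is the molecular weight of GSH, ht is hematocrit". The factor 0.075 is the estimated circulating volume in l/kg.

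The section Secondary outcomes lists GSH synthesis under oxidative stress. The section Tracer infusion protocol and blood sampling says that both FSR and ASR are to be calculated. The section Statistical analysis assigns the Mann-Whitney test to continuous measurements.

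**The concern.** An absolute rate is the fraction of the pool renewed per day times the size of the pool. Concentration, molecular weight, hematocrit and volume multiply to give that pool, so they belong in the numerator. The printed bracket puts them in the denominator with the 100, which is the only factor that should be there.

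A constant scale error would not matter to a rank test. This error is not constant: it depends on each infant's own GSH concentration and hematocrit, so it changes the order of the infants. Reduced oxidative stress is part of the trial hypothesis, and infants receive an 8-hour tracer infusion with arterial sampling to obtain these rates. Anyone who coded or replicated ASR from the published formula would get wrong values and possibly the wrong direction of a group difference.

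**Working it through.** **Inputs from the document (section Calculations).** FSR in %/d; conc in mmol/l packed erythrocytes; 307, the molecular weight, that is 307 mg/mmol; ht, dimensionless; 0.075 l/kg. The stated unit of ASR is mg/(kg·d).

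**Inputs assumed.** The document gives no values for FSR, conc or ht. For illustration: FSR 30 %/d, conc 2 mmol/l (range 1.5–2.5) and ht 0.45 as a fraction (range 0.40–0.50).

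**1. Units.**
- Pool = conc × 307 × ht × 0.075: (mmol/l) × (mg/mmol) × (l/kg) = mg/kg.
- FSR/100 has the unit 1/d.
- Printed form, (FSR/100) / pool: (1/d) / (mg/kg) = kg/(mg·d). This does not reproduce the stated unit.
- Product form, (FSR/100) × pool: (1/d) × (mg/kg) = mg/(kg·d). This does.

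**2. Size of the discrepancy.**
- Pool = 2 × 307 × 0.45 × 0.075 = 20.72 mg/kg.
- Product form: 0.30 × 20.72 = 6.22 mg/(kg·d).
- Printed form: 0.30 / 20.72 = 0.0145.
- Ratio of product to printed = pool² = 20.72² ≈ 429, whatever the FSR.
- Lower end (conc 1.5, ht 0.40): pool 13.82, ratio 191. Upper end (conc 2.5, ht 0.50): pool 28.78, ratio 828.

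**3. Direction.** Hold FSR and ht fixed and raise conc by 20%.
- Product form: × 1.20, so ASR is 20% higher.
- Printed form: × 1/1.20 = 0.833, so ASR is 17% lower.

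**4. Effect on ranks.** On the log scale the product form is log FSR + log pool and the printed form is log FSR − log pool, apart from constants. Assume FSR, conc and ht are independent and log-normal, with log-scale SDs s_F, s_C and s_H. Then:
- Correlation on the log scale: r = (s_F² − s_P²) / (s_F² + s_P²), with s_P² = s_C² + s_H².
- Rank correlation: (6/π) × arcsin(r/2).

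Take s_H = 0.10, s_F from 0.2 to 0.4 and s_C from 0.1 to 0.3.
- Best corner (s_F 0.4, s_C 0.1): r = (0.16 − 0.02) / (0.16 + 0.02) = 0.778; rank correlation +0.76.
- Worst corner (s_F 0.2, s_C 0.3): r = (0.04 − 0.10) / (0.04 + 0.10) = −0.429; rank correlation −0.41.

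So the two versions never rank infants identically over this range, and in part of it they rank them in broadly opposite order.

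**The case against.** The strongest reply is that this is a typographical slip. The unit label on the left of the same equation lacks its closing bracket, so brackets in that line are already unreliable. The definitions around the equation admit only the product form, and a careful reader can recover it from the same section. A laboratory that did code the printed form would, under the assumed inputs, see 0.0145 where it expected about 6, and would probably notice.

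Much of this stands. It bears on severity and does not make the equation right. The bracket on the right-hand side is balanced and encloses all five factors, and no other section gives a different form. Nor is this a detail left to a fuller document: the article states a specific formula and states it wrongly.

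Two stronger readings are tempting, and the document supports neither.
- A reader might infer that the trial's ASR values are, or will be, computed wrongly. Nothing shows which form the laboratory or the analysis uses, so the harm is conditional on the printed form being followed.
- A reader might infer that ASR is itself a named endpoint, or that the whole oxidative-stress comparison is at risk. The section Secondary outcomes names GSH synthesis, not ASR. FSR comes from equation 1 and does not depend on equation 2. Neither do GSH concentration, non-protein-bound iron, isoprostanes and 8-oxo-dG.

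**Conclusion.** The point holds for the equation as printed. The unit contradiction and the reversed dependence on concentration and hematocrit follow from the article's own definitions and need no assumed values. The sizes are illustrative and conditional on the printed form being coded: the factor of about 430 (190 to 830) rests on the assumed conc and ht, and the rank correlations of about +0.76 to −0.41 rest on the assumed spreads, log-normality and independence.

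The reach is limited to ASR, one of the two synthesis measures behind one secondary outcome. The primary outcome and the sample size are untouched. Severity is minor to moderate: a probable bracket error that is easy to correct, but one that changes more than the scale if followed.

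**What to change.** Print equation 2 as ASR (mg/(kg·d)) = (FSR/100) × conc × 307 × ht × 0.075, and close the bracket in the unit label on its left-hand side. Confirm that the laboratory spreadsheet or analysis code uses this product form, for example by running one infant's values by hand. If any ASR has already been computed from the printed form, recompute it from the stored FSR, concentration and hematocrit. The cost is one corrected line and one check; no data, sampling or design changes.

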### Oxidative stress markers

Oxidative stress markers in plasma and urine will be determined within 24 h of birth, on postnatal day 6 and on postnatal day 28.

#### Non-protein bound iron (NPBI)

Blood samples, drawn from an arterial catheter or via a heel prick, will be collected in heparinized microtainers and immediately placed on melting ice. After centrifugation at 3,500 × g for 10 min, the plasma fraction will be removed from the lower layer and stored at −80 °C until further analysis. Plasma samples will be shipped on dry ice to the University of Siena (Siena, Italy), where the NPBI will be determined according to previously described methods [15].

#### Isoprostanes and 8-hydroxy-2’-deoxyguanosine (8-oxo-dG)

Urine will be collected by placing gauze in the infants’ diapers. After centrifugation at 2,800 × g for 5 min, the urine will be stored at −80 °C until further analysis. Urine samples will be shipped on dry ice to the University Hospital LA Fe (Valencia, Spain), where the urinary isoprostane and 8-oxo-dG will be determined according to previously described methods [16].

### Statistical analysis

Power calculation based on the incidence of BPD shows that, with an incidence of 30% and an expected reduction of 15%, 100 infants per group will be needed to find a statistically significant difference with an α of 0.05 and a power of 0.80. Differences between groups will be assessed using the Mann-Whitney test for continuous measurements and the chi-square test for categorical measurements (*p* < 0.05).

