**Methods/design:**

In this double-blind, randomized controlled trial, 200 very preterm infants with a gestational age < 32 weeks will be randomized to start resuscitation after birth with either 30% or 65% oxygen. The FiO_2_ will be adjusted based on oxygen saturation measured by pulse oximetry (SpO_2_) and pulse rate (which should be over 100 beats per minute) in order to achieve a target SpO_2_ of 88–94% at 10 min of life. The FiO_2_ and pulse oximetry data will be continuously recorded.

The primary outcome is survival without bronchopulmonary dysplasia, as assessed by a physiological test at 36 weeks postmenstrual age. The secondary outcomes include the time to achieve SpO_2_ > 88%, Apgar score at 5 min, cumulative O_2_ exposure, oxidative stress (as determined by glutathione synthesis and oxidative stress markers), retinopathy of prematurity, brain injury and neurodevelopmental outcome at 2 years of age.

This study will provide insight into determining the appropriate initial FiO_2_ to start resuscitation of very preterm infants.

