### Outcome parameters

#### Primary outcome

Survival without BPD at 36 weeks postmenstrual age (PMA).

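### The sample size is justified for BPD alone, but the primary outcome is survival without BPD, so the stated 0.80 power does not apply to the primary test

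*Protocol article*

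**What the plan says.** The Abstract (Methods/design) states: "The primary outcome is survival without bronchopulmonary dysplasia, as assessed by a physiological test at 36 weeks postmenstrual age". The Primary outcome section names the same outcome. The event that counts as failure is therefore death or BPD.

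The only power statement is in the Statistical analysis section. It begins "Power calculation based on the incidence of BPD shows that", continues "with an incidence of 30% and an expected reduction of 15" per cent, and concludes that "100 infants per group will be needed to find a statistically significant difference" "with an α of 0.05 and a power of 0.80". The Abstract carries the total: "200 very preterm infants with a gestational age < 32 weeks will be randomized". The test named for categorical outcomes is the chi-square test at p < 0.05.

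Death appears in the Trial design section as a reportable serious adverse event. Nowhere does the article give a mortality rate, a rate for death-or-BPD or an assumed effect on death. It also does not say whether the 30% applies to all randomized infants or to survivors, or whether the 15% reduction is absolute or relative.

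**The concern.** The outcome used to set the sample size is one component of the outcome to be tested. Adding deaths changes the calculation in two ways. The failure rate in both groups moves up towards 50%, where the binomial variance is larger. If treatment acts only on BPD among survivors, the absolute difference in the composite also shrinks, because infants who die cannot benefit.

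What is at stake is how the result will be read. A null primary comparison would be judged against a claimed power of 0.80 that was not calculated for that comparison. Type I error and the validity of the test are not affected.

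This is not a detail dropped when the full protocol was condensed. The article prints a complete power statement, with endpoint, rate, effect, alpha, power and sample size, and that statement is for a different endpoint.

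**Working it through.** **Inputs from the article.** Reference BPD rate 30%; reduction 15%, read as absolute (30% v 15%); 100 per group; α = 0.05, taken as two-sided because the named test is chi-square at p < 0.05; stated power 0.80.

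**Input not in the article.** Mortality before 36 weeks, *d*. It is assumed, and shown at 1%, 5%, 10%, 15% and 20%.

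**Step 1: the plan's own figure, BPD only.** With pooled variance,

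n = [1.96·√(2p̄(1−p̄)) + 0.8416·√(p₁(1−p₁) + p₂(1−p₂))]² / (p₁−p₂)²

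Here p₁ = 0.30, p₂ = 0.15 and p̄ = 0.225. The numerator is (1.96 × 0.5906 + 0.8416 × 0.5809)² = 2.711, and 2.711 / 0.0225 = 120.5, so 121 per group. Other two-sided formulas give 118 (unpooled), 119 (arcsine) and 134 (continuity-corrected). None gives 100.

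Power at 100 per group is Φ[(0.15 × 10 − 1.96 × 0.5906) / 0.5809] = Φ(0.59) = 0.72. Exact enumeration of the uncorrected chi-square test gives 0.73. A one-sided test would need 95 per group and give 0.82 at 100, but the article does not state one. Read as a relative reduction (30% v 25.5%), power at 100 per group would be 0.11.

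The baseline before any deaths are counted is thus 0.72–0.73, not 0.80.

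**Step 2: the primary outcome, failure = death or BPD.** The control rate is d + (1−d) × 0.30 in all three cases:

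- **A.** Equal mortality, BPD among survivors 30% v 15%: treated rate = d + (1−d) × 0.15.
- **B.** The composite falls by a full 15 points: treated rate = control − 0.15.
- **C.** As A, but treatment also halves mortality: treated rate = d/2 + (1−d/2) × 0.15.

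Power is by exact enumeration of the chi-square test, 100 per group, two-sided 0.05.

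| Assumed d | Control | Treated, A | Difference, A | Power A | Power B | Power C |
|---|---|---|---|---|---|---|
| 1% | 30.7% | 15.9% | 14.9 points | 0.71 | 0.72 | 0.74 |
| 5% | 33.5% | 19.3% | 14.3 points | 0.63 | 0.68 | 0.77 |
| 10% | 37.0% | 23.5% | 13.5 points | 0.55 | 0.65 | 0.81 |
| 15% | 40.5% | 27.8% | 12.8 points | 0.48 | 0.62 | 0.84 |
| 20% | 44.0% | 32.0% | 12.0 points | 0.42 | 0.60 | 0.87 |

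If the 30% and 15% are instead rates per randomized infant, with equal deaths added to each group, power is 0.67, 0.63 and 0.59 at 5%, 10% and 15% mortality, close to case B.

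**Step 3: separating the two causes.** The fall from 0.80 to about 0.73 is arithmetic and would exist without any deaths. From 0.73, over 5–15% mortality, the change of endpoint takes off about 10 to 25 points in case A (0.73 − 0.63 to 0.73 − 0.48) and about 5 to 11 points in case B (0.73 − 0.68 to 0.73 − 0.62). Correcting the arithmetic alone, to 121 per group, would not give 0.80 for the composite in case A, where 149, 181 and 216 per group are needed at 5%, 10% and 15% mortality.

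**The case against.** A reader might infer that the trial's real power is about 48–68%. The article does not support that as a fact. The range needs a mortality rate that the article does not give and an assumption about how treatment affects death. This objection stands, which is why every composite figure above is labelled an illustration.

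Three further objections have weight.

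- **Adding death need not reduce power.** The Background hypothesizes better outcome in general, not only less BPD. If mortality is halved alongside the full fall in BPD, power exceeds the BPD-only baseline (case C). This stands as arithmetic. It does not rescue the stated 0.80, because the sample-size statement mentions no effect on death, and a halving of mortality is a large effect to leave unstated.
- **Mortality may be low.** The Discussion expects the included infants, who will have received prenatal steroids, to show less morbidity than very preterm infants at large. At 1% mortality the loss from the mismatch is only about 1 to 2 points. This also stands, and it is a reason to write the assumed rate down.
- **Much of the drop from 0.80 belongs to the separate arithmetic shortfall.** This stands. The 0.73 baseline must be shown so that the whole drop is not put down to the endpoint.

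The 30% might also be taken as the composite rate itself. The words of the sample-size statement say BPD, and on that reading power would still be about 0.72–0.73.

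**Conclusion.** The point holds as a mismatch of endpoints: the stated power refers to BPD, the primary test concerns death or BPD, and nothing in the article reconciles the two. The stated 0.80 therefore does not describe the primary comparison, and read as 30% v 15% two-sided it does not describe BPD either.

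The size of the shortfall for the primary outcome cannot be read from the article. Over an assumed 5–15% mortality, power is about 0.63–0.48 with equal deaths and an effect confined to BPD among survivors. It is about 0.68–0.62 with a 15-point fall in the composite, and about 0.77–0.84 if deaths are also halved. That spread comes entirely from inputs the plan leaves unstated. The mismatch is certain; any single power figure for the composite is conditional.

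**What to change.** Restate the power in the Statistical analysis section for death-or-BPD at 100 per group. Give the assumed mortality, the resulting control rate of the composite, the assumed effect on death, the detectable absolute difference, and whether the test is one- or two-sided. Say whether the 30% refers to survivors or to all randomized infants, and that the 15% is an absolute reduction if that is meant. Keep the BPD-only calculation if wanted, corrected to about 0.72–0.73 at 100 per group and labelled as referring to a component of the primary outcome.

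The assumptions should come from information available before unblinding, and the text should say when the restatement was made, since the Trial status section reports that enrolment is under way. The cost is a rewritten paragraph and a less favourable stated figure. The endpoint, test and number of infants stay as they are.

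### The sample size does not deliver its stated 80% power: 30% versus 15% with 100 infants per group gives about 73% with a two-sided test at 0.05, and 80% needs about 121 per group

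*Protocol article*

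**What the plan says.** The sample size is justified in one sentence of the Statistical analysis section of the protocol article. It rests on BPD incidence, "with an incidence of 30% and an expected reduction of 15" per cent, and states that "100 infants per group will be needed to find a statistically significant difference with an α of 0.05 and a power of 0.80". The abstract gives the matching total: "200 very preterm infants with a gestational age < 32 weeks will be randomized".

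The next sentence of the same section sets the analysis: "the chi-square test for categorical measurements", with significance at p < 0.05. The article does not say whether the α in the power calculation is one-sided or two-sided, or whether the 15% is absolute or relative.

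**The concern.** The sentence gives every input and the result, so it can be checked directly. The well-known two-proportion formula for 30% versus 15% at two-sided 0.05 gives a figure well above 100 per group.

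This is the article's only justification for 200 infants. If the power is overstated, a non-significant result would be reported as coming from a trial with a one-in-five chance of missing the planned effect, when the chance is more than one in four. Type I error, the estimate and its confidence interval are not affected.

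**Working it through.** **Inputs.** All come from the Statistical analysis section: p₁ = 0.30; p₂ = 0.15 (15% read as an absolute reduction); α = 0.05; power 0.80; 100 per group, hence equal allocation; chi-square test at p < 0.05. The mean proportion is (0.30 + 0.15)/2 = 0.225.

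**Step 1. Try to reproduce 100 per group, two-sided.** The pooled-variance formula is

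n = [z₁₋α/₂ √(2p̄(1−p̄)) + z₁₋β √(p₁(1−p₁) + p₂(1−p₂))]² / (p₁−p₂)²

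- √(2 × 0.225 × 0.775) = √0.34875 = 0.5906; times 1.960 = 1.1575
- √(0.30 × 0.70 + 0.15 × 0.85) = √0.3375 = 0.5809; times 0.8416 = 0.4889
- n = (1.1575 + 0.4889)² / 0.0225 = 2.7106 / 0.0225 = 120.5, so **121 per group** (242 in total)

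Other two-sided versions do not reach 100 either: 118 with unpooled variance, 119 with the arcsine transformation, 134 with continuity correction.

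**Step 2. Power with the planned 100 per group.**

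- z = (√100 × 0.15 − 1.1575) / 0.5809 = 0.3425 / 0.5809 = 0.590, so power is **72.2%**
- Exact binomial enumeration of the uncorrected chi-square test: **72.9%**
- The same enumeration at 121 per group: 80.9%
- As a sensitivity figure only, a Yates-corrected test at 100 per group: 66.8%

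**Step 3. Other readings that might explain the figure.**

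| Reading | n per group for 80% power | Power at 100 per group |
|---|---|---|
| 30% v 15%, two-sided 0.05 | 121 | 72.2% |
| 30% v 15%, one-sided 0.05 | 95 | 81.9% |
| 30% v 15%, one-sided 0.05, continuity-corrected | 108 | not computed |
| 30% v 25.5% (relative 15%), two-sided 0.05 | 1,554 | about 11% |

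For the one-sided row, 1.645 replaces 1.960: (0.9714 + 0.4889)² / 0.0225 = 94.8. This is the only route that comes near 100. The relative reading is so far off that the authors must have meant an absolute reduction.

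**Step 4. What 100 per group can detect.** With 30% in one arm, the pooled formula reaches 80% two-sided power at 13.7% in the other, a difference of 16.3 points. Exact power is 79.3% at 14.0% and 81.0% at 13.7%, so 30% versus about 14% is a fair summary.

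**The case against.** The best defence is that the calculation was one-sided. The article does not state the sidedness of α, and the Background gives a directional hypothesis in favour of the 30% arm. One-sided, 94.8 per group is needed, and an assumed 5% allowance for losses (94.8/0.95 = 99.8) would give exactly 100. On that view the arithmetic is sound and the fault is an undeclared choice. This may well be the origin of the number, but it does not rescue the sentence. No one-sided test is declared, and the chi-square test planned in the same section rejects in either direction. The stated power would then belong to a test the trial does not plan to use. The allowance is not in the article either.

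The second defence is that the shortfall is small: about 7 points of power, or a detectable rate of about 14% instead of 15%. That is a fair description of the size, and nothing in the conduct or analysis of the trial has to change because of it. The stated figure is still wrong.

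Three further points on the other side stand. The continuity-corrected figures are variants and not the test as written. The relative reading serves only to show that the reduction must be absolute. The lack of a stated allowance for missing outcomes is no fault in an article that condenses a fuller protocol.

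It is also right that the calculation concerns BPD alone, whereas the primary outcome is survival without BPD. If deaths raise the event rate and the difference stays at 15 points, power falls further. Assumed rates of 35% v 20% and 40% v 25% give exact power of 67% and 63% at 100 per group. The corrected figure should therefore name the endpoint it applies to.

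**Conclusion.** The concern holds. For an absolute reduction in BPD from 30% to 15%, two-sided α of 0.05 and equal groups, 80% power needs 121 infants per group by the pooled formula (118 unpooled). That is about 21 more per group and 42 more in total than planned. With 100 per group, power is 72% to 73% and the type II error about 27%.

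The conclusion rests on two readings: that the reduction is absolute, which favours the plan, and that the test is two-sided, which follows from the planned chi-square test at p < 0.05. No two-sided version of the calculation gives 100. A one-sided origin is possible but would put the power statement at odds with the planned analysis. The sentence needs correcting on either account.

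**What to change.** Keep the 200 infants and replace the power sentence in the Statistical analysis section. Suggested content: for an absolute reduction in BPD from 30% to 15%, 100 infants per group give about 73% power with a two-sided chi-square test at 0.05; about 80% power corresponds to 30% versus about 14%; 80% power for 30% versus 15% would need about 121 per group. Say plainly that these figures are for BPD and not for the composite of death or BPD.

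If the original calculation was one-sided, say so as the explanation of the number. Moving to a one-sided test while the trial is enrolling would be a poor way to make the two agree.

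The cost is one sentence and a less favourable power figure. No extra infants are needed, and the planned analysis does not change.

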### Subjects

The inclusion criteria are infants with a GA < 32 weeks born at the Erasmus MC-Sophia Children’s Hospital. Assessment of the GA will be based on early fetal ultrasonography or on the date of the last menstrual period. The exclusion criteria are any known major congenital malformations, chromosome defects, or metabolic, endocrine or renal disorders.

Because this study involves an acute intervention at birth, written informed consent will be obtained antenatally. All mothers admitted to Erasmus MC-Sophia Children’s Hospital at risk for preterm delivery before 32 weeks of gestation (e.g., premature labor, preeclampsia, intrauterine growth retardation) will be approached for participation in the study. When parents have consented to participate in the study and there has been an actual preterm delivery, the preterm infant will be included at birth.

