### Research setting and randomization

The Erasmus MC-Sophia Children’s Hospital has six resuscitation units, which have been modified for this study by adding an additional oxygen blender (PM5200, Precision Medical Inc., Northampton, PA, USA) (Figure 1). This additional oxygen blender is not visible to the physician and will be randomized after each inclusion to either 30% or 65% oxygen using a computer-generated list.

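### The primary test is an unadjusted chi-square although gestational age is known for every infant; adjusting for it would gain precision at almost no cost

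*Protocol article*

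**What the plan says.** The Statistical analysis section of the protocol article assigns tests by type of variable: "Differences between groups will be assessed using the Mann-Whitney test for continuous measurements and the chi-square test for categorical measurements". The primary outcome is a yes/no outcome at 36 weeks postmenstrual age, so it falls under "the chi-square test for categorical measurements". No covariate or stratified test is named.

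The same section gives the design figures: "with an incidence of 30% and an expected reduction of 15%, 100 infants per group will be needed", "with an α of 0.05 and a power of 0.80". The Abstract gives the matching total of 200.

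On GA, the Subjects section states: "The inclusion criteria are infants with a GA < 32 weeks". It gives no lower limit. It also says how GA is determined, so every randomised infant has a value that precedes treatment.

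On allocation, the section on research setting and randomization says that the hidden blender "will be randomized after each inclusion to either 30% or 65% oxygen using a computer-generated list". No stratification factor is named.

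**The concern.** GA is a plausible strong predictor of death or BPD, it costs nothing to use, and the plan uses it neither in the allocation nor in the test. Because each blender is set before the next infant's GA is known, the mechanism as described cannot match allocation to GA. The analysis is then the only place where GA can be taken into account.

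This matters more here than in a trial with power to spare. A two-sided chi-square with 100 infants per arm has less than the stated 80% power at the planned rates (see the calculation below). If a strong predictor is left out, variation that could be explained stays as noise in the treatment comparison.

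**Working it through.** **Inputs from the article.** Event rates 30% and 15% (a 15-point absolute reduction), 100 per arm, alpha 0.05, power 0.80. Sidedness is not stated; two-sided is taken as usual for a chi-square. The rates are given for BPD and are used here for death or BPD, because the article gives no rate for the composite.

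**Inputs that are assumptions.** The article gives neither the spread of GA nor GA-specific rates of death or BPD, so both are assumed and varied.

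**Step 1: the plan's own figure.** Pooled-variance formula, with mean rate (0.30 + 0.15)/2 = 0.225:

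n = [1.960 × √(2 × 0.225 × 0.775) + 0.842 × √(0.30 × 0.70 + 0.15 × 0.85)]² / 0.15²
= [1.960 × 0.5906 + 0.842 × 0.5810]² / 0.0225 ≈ 121 per arm.

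The stated 100 is not reproduced. Other two-sided versions give 118 (unpooled), 119 (arcsine) and 134 (continuity-corrected). One-sided, the pooled formula gives 95.

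Power at 100 per arm, two-sided: Φ[(0.15 × √100 − 1.960 × 0.5906)/0.5810] = Φ(0.59) = 0.72. One-sided it is 0.82.

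**Step 2: how predictive GA must be.** As a rough variance argument, for 100 adjusted infants per arm to carry the information of 121 unadjusted ones, GA must explain about 1 − 100/121 = 17% of the outcome variance.

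**Step 3: simulation.** Trials of 100 per arm were simulated with the overall event rates held at 30% and 15%. The Pearson chi-square was compared with a logistic regression on arm and continuous GA.

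*Assumed GA 24–32 weeks, mean 28.8, SD 1.9; 4,000 trials per row; likelihood-ratio test for arm:*

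| OR per week of lower GA | Same, per week of higher GA | Chi-square power | GA-adjusted power |
|---|---|---|---|
| 1.00 | 1.00 | 0.736 | 0.740 |
| 1.25 | 0.80 | 0.747 | 0.763 |
| 1.50 | 0.67 | 0.720 | 0.767 |
| 1.75 | 0.57 | 0.723 | 0.807 |
| 2.00 | 0.50 | 0.743 | 0.847 |
| 2.50 | 0.40 | 0.735 | 0.897 |

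The Monte Carlo standard error is about 0.7 points. The overall rates are fixed, so the spread in the chi-square column is essentially simulation noise, and gains are best read within a row. With no treatment effect, the rejection rate was 0.048–0.056 for the chi-square and 0.045–0.057 for the adjusted model.

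*Assumed GA 24–31 weeks, SD 2.1; 2,500 trials per scenario:* chi-square power 73% throughout. Adjusted power was 75%, 76%, 80% and 86% at odds ratios of 0.8, 0.7, 0.6 and 0.5 per week of higher GA, with type I error 4–5%. Repeat runs under these assumptions gave 71–74% for the chi-square and 74–75%, 76–77%, 82% and 85–86% for the adjusted test.

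**Step 4: the scale of the estimate.** The planned rates imply an unadjusted odds ratio of (0.15/0.85)/(0.30/0.70) = 0.41. At an odds ratio of 2.0 per week of lower GA, the same two rates correspond to a GA-conditional odds ratio of 0.31. The adjusted odds ratio is thus a different quantity, whereas a GA-standardised risk difference stays on the 15-point scale of the power calculation.

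**The case against.** The strongest objection is that nothing here is an error. A chi-square is a valid test of a randomised binary outcome, and its type I error is nominal in every simulation. That stands, and it makes the point one of efficiency.

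A second objection is that an article leaves covariates to the full protocol or analysis plan. That stands in part: an adjusted analysis may exist in a document not shown. But the article does more than stay silent. It names the test, and the point concerns that stated choice.

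A third is that the gain rests on an undocumented figure. This also stands. The article supports a link between lung immaturity and respiratory outcome only indirectly, in its discussion of prenatal steroids. At the weak end of the assumed range the gain is only about 2 points.

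Three stronger readings are tempting and are not supported:

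- *A reader might infer that GA will be unbalanced.* Randomisation balances it in expectation; only stratification is ruled out by the mechanism described. With SD 2.11, the standard error of the difference in mean GA is 2.11 × √(2/100) = 0.30 week. A 2-SE imbalance of 0.6 week would by itself produce a risk difference of about 2.7 to 5.8 points under odds ratios of 0.8 to 0.5. That is roughly a 1-in-20 event, and the chi-square's error rate already allows for it.
- *A reader might infer that adjustment restores the stated 80% power.* It does so only if GA is strongly predictive.
- *A reader might infer that siblings from multiple births invalidate the test.* The article does not mention multiple births or how they would be allocated. If siblings are randomised independently, type I error is not inflated on average, so no harm is shown.

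**Conclusion.** The point holds as an avoidable loss of precision in the primary comparison. It is not bias, and it does not make the planned test invalid. At the planned rates, with 100 infants per arm and a two-sided test, power is about 72–73% unadjusted and about 74–86% with GA in the model, for assumed odds ratios of 0.8 to 0.5 per week. It reaches 80% only at about 0.6 per week or stronger.

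The direction is secure across two assumed GA distributions. The size is not, because it depends on a GA effect and a GA spread that the article does not give. The mismatch between 100 and about 121 per arm is a separate matter that adjustment does not correct. If one-sided testing was intended, power at 100 per arm is already 0.82; adjustment would then add precision but would not be making up a shortfall.

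**What to change.** Before unblinding, pre-specify as the primary analysis a logistic regression of death or BPD on treatment arm and GA in weeks. Report the GA-standardised risk difference with its 95% confidence interval, so that the result reads on the same scale as the power calculation. Keep the chi-square as a supportive unadjusted result.

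Apply the same GA-adjusted model to the binary secondary outcomes, retinopathy of prematurity and brain injury, and to those only. A logistic model does not fit the continuous ones, such as time to target saturation or glutathione synthesis, and the simulations above do not cover any secondary outcome.

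The cost is a few lines of analysis wording. No new data, infants or procedures are needed, since GA is already established for eligibility. At the planned rates the model has 100 × 0.30 + 100 × 0.15 = 45 events for two terms, which is adequate. The Trial status section says that enrolment is still under way, so the change can be dated before any result is known. The same adjustment added after an imbalance had been seen would look data-driven. If a full protocol or analysis plan already specifies GA adjustment, the two descriptions need only be aligned.
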